### Withdrawal

2.6

Participation is voluntary, and participants can withdraw consent at any time. Reasons for withdrawal will be documented.

#### Short-term VR intervention trial

2.6.1

In the event of any discomfort, including dizziness or nausea, experienced by a participant during the VR intervention, the intervention is promptly terminated. The participant is then given a two-minute break for recovery. If the discomfort continues post-rest, the participant is advised to withdraw from the study after a consultation.

#### Long-term real environment intervention trial

2.6.2

Being lost to follow-up does not constitute withdrawal from the study. Research staffs will make efforts to re-engage participants for future assessments. For instance, if a participant is unreachable at the 12-month check-in, this is noted as a missed appointment, and attempts will be made to reach them for the 24-month follow-up.

### Blinding

2.7

#### Short-term VR intervention trial

2.7.1

Researchers from the survey group collect epidemiological data and assess participants’ cognitive function through questionnaires. Survey group researchers are blinded to the group allocation. The VR intervention process cannot be completed independently by participants. VR operators need to assist in the procedure and guide participants to fully engage with the VR scene. Therefore, it is not feasible to blind either the participants or the VR operators. To minimize bias, cognitive outcome assessments will be conducted by survey group researchers who are not involved in the VR intervention.

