Preparation Phase: first, researchers provide a concise introduction to the study procedures. Participants rest for 5 min, and heart rate and blood pressure are measured using an Omron medical electronic blood pressure monitor (HBP-1300). Then, baseline data are collected through a questionnaire survey. The structured questionnaire includes general demographic characteristics such as age, gender, height, weight, ethnicity, education level, marital status, and income. It also includes lifestyle behaviors such as smoking, alcohol consumption, and physical activity, medical histories such as hypertension, diabetes, and cardiovascular disease, and medication history. An assessment of mental health status is conducted using the Center for Epidemiologic Studies Depression Scale (10-item, CESD-10). Finally, cognitive scores are assessed using the Digit Symbol Substitution Test (DSST) and the Backward Digit Span (BDS) scale. After the measurements, researchers provide the VR headset to participants and allow them to adapt and learn basic operations for up to 5 min. All VR devices look the same shape and color.Stress Phase: participants are exposed to a cluttered living environment through VR, with background noise from bustling traffic and mechanical devices. Then they undergo stress-inducing tests, including a memory test and an arithmetic test. The stress phase lasts for 5 min. After this phase, cognitive scores (DSST/BDS), heart rate, and blood pressure are re-measured.VR Intervention Phase: participants will engage in a 10–15 min of VR scenario intervention according to their group allocation. Depending on their groups, some participants may simulate activities such as walking indoors, opening doors, pulling curtains, watering plants, or feeding fish. After completing the VR intervention, cognitive scores (DSST and BDS), heart rate, and blood pressure are measured again. Additionally, the Environmental Semantics Differential Scale (SD) and the Restoration Scale (RS) are also evaluated.

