### Randomization

2.10

Randomization is conducted by a computer-generated list of random numbers made by independent statisticians without any clinical involvement in the study. The block randomization sequence is generated using SAS 9.4 software (PROC PLAN). The randomized block sizes are set to 8 and 16 for the short-term VR intervention trial and 2 and 4 for the long-term real environment intervention trial. After obtaining eligible patient consent, allocations are determined using sequentially numbered sealed envelopes containing information disclosing the type of intervention to be applied. Additionally, group assignments will be concealed until the intervention begins.

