#### Short-term VR intervention trial

2.14.1

To ensure that participants’ attention is maximally directed towards the biophilic elements during the VR experience, VR operators explain the VR environment to participants and guide them in observing the biophilic elements during the experience.

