This study also has several limitations. First, the study is conducted in a single center and focuses only on elderly diabetics, which limits the generalizability of the findings. Second, the VR scene contains many furnishings, which may cause participants to ignore specific intervention elements assigned to them. To avoid this issue, researchers in the VR group assist subjects in noticing the assigned elements through verbal guidance and cues. Third, the Mini-Mental State Examination (MMSE) (Tsoi et al., 2015) and MoCA (Nasreddine et al., 2005) are widely used scales that comprehensively assess cognitive function (Islam et al., 2023; Miura et al., 2024), however, they lack sensitivity to detect immediate cognitive changes. Therefore, we use the DSST and BDS scales to evaluate cognitive scores in the short-term VR intervention trial. The DSST primarily assesses working memory and processing speed, while the BDS focuses on memory capacity and attention. Although they are not as comprehensive as MMSE and MOCA, they are more sensitive to short-term cognitive changes and are widely used in cognitive assessments (Cukierman-Yaffe et al., 2020; Greendale et al., 2021; Tian et al., 2015).

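### The need for operators to assist does not rule out masking VR-trial participants to the hypothesis and to which scene is the control

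*Protocol article*

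**What the plan says.** Section 2.7.1 of the protocol article (Blinding, short-term VR trial) gives two premises: "The VR intervention process cannot be completed independently by participants", and "VR operators need to assist in the procedure and guide participants to fully engage with the VR scene". From these it concludes: "Therefore, it is not feasible to blind either the participants or the VR operators". Its safeguard is that "cognitive outcome assessments will be conducted by survey group researchers who are not involved in the VR intervention", and those researchers are blinded to allocation.

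Other sections bear on the same point:

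- Section 2.10 adds that "group assignments will be concealed until the intervention begins".
- Section 2.5.1 shows every participant the same cluttered scene in the stress phase. Each then receives a "VR scenario intervention according to their group allocation", after which DSST, BDS, the Semantic Differential (SD) and the Restoration Scale (RS) are administered.
- Section 2.14.1 says that "VR operators explain the VR environment to participants and guide them in observing the biophilic elements during the experience". The limitations in the Discussion repeat that "researchers in the VR group assist subjects in noticing the assigned elements through verbal guidance and cues".

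**The concern.** The conclusion covers two groups, but the reasoning supports it for only one. An operator who runs the session must know the scene. A participant who is helped through it need not know what the other scenes contain, which one is the control, or what result is hoped for. Section 2.7.1 treats all of this as one question and sets it aside.

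The comparison at stake is the one that chooses the long-term intervention. Under section 2.12.1, each of the seven biophilic scenes is compared with a single control on post-intervention cognitive scores. Scenes reaching p < 0.1 become candidates, and the candidate with the largest adjusted difference goes forward. DSST is a timed test and BDS a recall test, so both respond to effort and attention. If participants in the biophilic arms expect benefit, or receive more engaging guidance than those in the blank arm, all seven comparisons can move together against the one control.

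**Working it through.** The plan states no figure on this point, so there is none to reproduce. The check is mainly textual, followed by an illustration of size.

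**1. Does the reason reach participants?** The premises in 2.7.1 are that help is needed and that guidance is given. They imply that the operator knows the scene and that participants have their attention drawn to its contents. They do not imply that participants must know the comparator or the hypothesis. Section 2.7.2, on the long-term trial, uses a reason that does fit participants (the elements are easy to recognise). Section 2.7.1 does not use it.

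**2. What could be masked?** The headsets look alike in all arms (2.5.1), and the control is a tidy VR house without biophilic elements (2.5.1.1). Each participant sees the common cluttered scene and one allocated scene, so nobody sees a blank and a biophilic scene side by side. Objects in the allocated scene are visible and cannot be masked. The role of that scene in the trial can be.

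**3. Is guidance balanced?** Sections 2.14.1 and 3 describe guidance directed at the biophilic elements. The blank scene has none, and the article describes no matched guidance for it.

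**4. Do the safeguards cover this?** Blinded assessors address assessor bias. Concealment ends when the intervention starts, and the decisive DSST and BDS measurements come afterwards. Neither acts on participant expectancy or differential attention.

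**5. Illustration of size.** Inputs from section 2.11.1: SD 1.2, planned difference 1.0 DSST point, 8 per group. From section 2.12.1: the p < 0.1 screen against control. Assumptions of this review: no true effect, one test (DSST), no covariates, pooled variance on 64 − 8 = 56 degrees of freedom, and a common shift δ in all seven biophilic arms.

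- Standard error of one comparison: 1.2 × √(2/8) = 0.6.
- Noncentrality: δ / 0.6.
- A scene passes favourably if its t statistic exceeds the upper 5% point on 56 df (two-sided 0.10, favourable side).
- One scene: noncentral t. At least one of seven: simulation with the shared control, 200,000 replicates.

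| Assumed δ (DSST points) | δ / 0.6 | One given scene passes | At least one of seven passes |
|---|---|---|---|
| 0 | 0 | 5.0% | 19.9% |
| 0.25 | 0.42 | 10.9% | 36.1% |
| 0.5 | 0.83 | 20.6% | 55.6% |
| 1.0 | 1.67 | 50.1% | 86.9% |

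The 19.9% in the first row comes from seven comparisons at p < 0.1 and has nothing to do with blinding. The part due to the assumed shift is the excess: 36.1 − 19.9 = 16.2 percentage points at 0.25, and 55.6 − 19.9 = 35.7 at 0.5.

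Only the ratio of δ to the SD matters. With an SD of 2.4 instead of 1.2, a shift of 0.5 gives the 36.1% row, so a larger true SD weakens the effect.

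**6. What a common shift cannot do.** It adds the same amount to all seven differences from control, so their order does not change. It acts only on whether scenes pass the screen.

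**The case against.** The strongest reply is that declaring participants unblinded is simply accurate. They see the objects, and operators talk to them about those objects. A reader might infer that the stated reason applies only to operators. That goes too far, because the guidance named in 2.7.1 is given to participants and, by 2.14.1 and the Discussion, points out the elements. This stands: full participant blinding is not available, and masking to hypothesis and comparator is a lesser measure.

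A reader might also infer that participants are told they have a healing or a blank scene. The article does not say what they are told, and the information sheet and operator script are not shown. Both the direction and the existence of an expectancy effect are therefore inferences. This stands too.

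Third, the consequences are bounded. SD and RS are secondary outcomes and play no part in the selection. The long-term trial is randomised separately against its own control, so a false pass in the VR trial does not by itself bias that trial's result. DSST and BDS are performance tests given by blinded staff. All of this stands and limits the point to the screen.

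Finally, withholding the hypothesis could seem to conflict with guided observation, which the protocol uses as quality control. It does not have to: guidance can stay if it is matched across arms and says nothing about expected benefit.

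None of this supplies the missing step in 2.7.1. Needing assistance is not a reason why participants must know the comparator or the hypothesis.

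**Conclusion.** The point holds in a limited form. The rationale in 2.7.1 does not justify forgoing partial masking of participants, and partial masking is feasible with look-alike headsets, a VR control scene and one allocated scene each. As written, unblinded participants and guidance with no counterpart in the blank scene leave the DSST and BDS comparisons with the single control open to expectancy and attention bias. The limitations in the Discussion do not mention it.

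The size is unknown. Under the planning SD of 1.2, 8 per group and no true effect, an assumed common shift of a quarter to a half of the planned 1.0-point difference would raise the chance of at least one favourable pass from 19.9% to between 36.1% and 55.6%. These figures depend on assumed shifts and on that SD. A reader might infer that the bias would pick the wrong scene or undermine the long-term result. The documents do not support that, since a common shift leaves the ranking unchanged and the long-term trial has its own randomised control. This is an inexpensive improvement, not a fatal flaw.

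**What to change.** Replace the conclusion in section 2.7.1 with text to this effect: *Operators are not blinded. Participants see the contents of their own scene, but until the final DSST, BDS, SD and RS are complete they are not told which scene serves as control or which elements are expected to help.*

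To support it:

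- Describe all scenes neutrally, as home interiors, in recruitment and information material.
- Keep the guided observation, but give it in all eight arms from a matched script of equal length. In the blank scene the operator points out ordinary furnishings.
- Optionally, ask each participant at the end which group they think they were in.
- Add residual expectancy bias to the limitations.

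Cost: an ethics notification for the changed information material, a rewritten operator script and a short debrief. No extra staff are needed. Masking remains partial, because participants see the objects in their own scene. If VR enrolment is already complete, three things can still be done: correct the rationale, report what participants were told, and state the limitation when the selection is presented.

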#### Long-term real environment intervention trial

2.7.2

Since biophilic elements are easily identifiable, only questionnaire administrators, outcome assessors, and data analysts will be blinded to the group allocation.

### Outcomes

2.8

#### Short-term VR intervention trial

2.8.1

Primary outcome: cognitive function, evaluated using the DSST and BDS scales.Secondary outcome: scores of the SD and the RS scales, as well as blood pressure and heart rate.

#### Long-term real environment intervention trial

2.8.2

Primary outcome: cognitive function assessed by the DSST and MoCA scales, as well as concentrations plasma of p-tau181, esRAGE and IL-6.Secondary outcome: the amount of physical activity, blood pressure, scores of GDS-15 and PSQI. Participants will be asked to report the number of days per week they engage in vigorous physical activity (VPA), moderate physical activity (MPA), and walking, along with the daily duration of these activities. The metabolic equivalents (METs) of each study subject will be assigned and calculated based on the above information (Deng et al., 2008), and the amount of physical activity is the sum of METs.

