**Methods:**

This is a single-center, randomized controlled trial, which includes a short-term VR intervention and a long-term real environment intervention. In the short-term intervention trial, 64 diabetic patients over 60 years old are randomly assigned to 1 of 7 intervention groups or a control group. All intervention groups are constructed by single or various combinations of the 3 indoor biophilic elements: natural decorative paintings, indoor potted plants, and ornamental fish. The primary outcome of the short-term intervention trial is the cognitive scores assessed by DSST and BDS. In the long-term intervention trial, 240 diabetic patients over 60 years old will be randomly assigned to either the intervention group or the control group. The biophilic elements in long-term intervention will be determined based on the results of the short-term VR intervention trial. The primary outcomes of the long-term intervention trial are cognitive scores measured by DSST and MoCA, as well as concentrations of plasma p-tau181, esRAGE, and IL-6.

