#### Long-term real environment intervention trial

2.12.2

The modified intention-to-treat population (mITT) will be used for statistical analysis. Missing values will be imputed using multiple imputation. Firstly, two sample t-tests (for continuous and normally distributed variables) and chi-square test (for categorical variables) will be conducted to assess the baseline equivalence between the intervention and control groups. Two sample t-tests will be used to compare whether cognitive scores are statistically different between two groups. Multiple linear regression will be used to demonstrate whether the intervention is statistically associated with cognitive scores after adjusting for potential confounders. Repeated measures ANOVA will be used to compare cognitive scores across groups. The potential confounders will be corrected in the mixed-effect model to determine the association between intervention and cognitive scores. If the intervention has a direct effect on cognitive function, longitudinal causal mediation analysis will be further used to clarify the mediating factors through which the intervention may affect cognition.

To explore the interaction of *APOE4* and the biophilic environment on cognition, we will perform stratified analysis according to groups to clarify the main effects of *APOE4* on cognitive function. Then, mixed models will be used to adjust for potential covariates and to elucidate the main effect of *APOE4* on cognitive function in each group. Finally, the interaction term between the *APOE4* and the intervention group will be included in the mixed-effects model to identify the effect of the genetic-environmental interaction on cognitive function.

In our study, all statistical tests are two-tailed, with a significance level of *p* < 0.05.

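### The long-term trial has five unordered primary outcomes, each tested at 0.05, with no success rule: if any one suffices, the false-positive risk is about 15–23% under assumed correlations

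*Protocol article*

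**What the plan says.** Section 2.8.2 (long-term trial) lists: "Primary outcome: cognitive function assessed by the DSST and MoCA scales, as well as concentrations plasma of p-tau181, esRAGE and IL-6". The abstract gives the same five and calls them outcomes in the plural. Neither place ranks the five, names a primary time point or says how many must be significant.

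Section 2.12.2 compares the cognitive scores between the groups in four ways:

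- an unadjusted t-test;
- a linear regression with covariates;
- an analysis over the visits, worded as "Repeated measures ANOVA will be used to compare cognitive scores across groups";
- a mixed model with covariates.

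None is called primary. The level is then fixed for the whole study at 0.05: "all statistical tests are two-tailed, with a significance level of" is how that closing sentence begins its rule. No adjustment, hierarchy or gatekeeping appears anywhere in the document.

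Three other places bear on the point:

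- **Section 2.5.2:** DSST is measured at 12 and 24 months. After baseline, MoCA and the plasma biomarkers are measured at 24 months only.
- **Section 2.11.2:** the trial is sized for one unspecified cognitive score at two-sided 0.05 with 90% power. This gives 99 per group, raised to 120 for about 20% loss.
- **Section 2.1:** the main objectives of the long-term trial are the effect on cognition and its modification by *APOE4*. Biomarkers are not mentioned there.

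**The concern.** Five equal primary outcomes and a flat 0.05 per test are both positive statements of the protocol. Taken together, they do not hold the trial's error rate at 5% unless a success rule is added. The natural reading of a list of primary outcomes is that a significant result on any of them supports the intervention, and nothing in the text rules that reading out.

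The choice among methods and visits for the cognitive scores adds to this, because the result to be reported as the primary one is not fixed. Section 2.12.2 also makes the mediation analysis conditional on an effect on cognitive function. With two scores, four methods and two DSST visits, that condition is undefined, so an uncontrolled positive result could lead on to claims about mechanism. The findings are meant to guide the design of living environments for older people with diabetes, so what counts as a positive trial should be settled before the data are seen.

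**Working it through.** **Inputs.** There are five primary outcomes (section 2.8.2 and abstract). Each is tested at two-sided 0.05 (section 2.12.2). Enrolment is 120 per group with about 20% loss (section 2.11.2). The documents give no correlations between the outcomes, so a common correlation ρ is assumed and varied.

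**The plan's own figures.** The protocol states no familywise error rate; its only error figure is 0.05 per test. Its sample size of 99 per group does not follow from the stated difference of 0.02 and SD of 0.017 in a plain two-group comparison: 2 × [0.017 × (1.960 + 1.282) / 0.02]² = 15.2, so 16 per group. That is a separate matter and does not affect this point. The detectable differences below are therefore in SD units and start from the evaluable number, not from the plan's assumed effect.

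**Step 1: any one of five, one test each.** With independent outcomes, 1 − 0.95⁵ = 0.226. For correlated outcomes, equicorrelated normal test statistics were simulated (1,000,000 draws), counting draws with any |z| > 1.96:

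| Assumed ρ | Five outcomes | DSST and MoCA only |
|---|---|---|
| 0 | 22.6% | 9.7% |
| 0.3 | 20.9% | 9.5% |
| 0.5 | 18.3% | 9.1% |
| 0.7 | 14.9% | 8.3% |
| 0.9 | 10.1% | 7.0% |

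The exact value for two independent outcomes is 1 − 0.95² = 9.75%. A less uniform assumption (0.4–0.6 between the cognitive scores, 0.1–0.3 among the biomarkers, 0.05–0.2 across the two sets) gives 20.8–22.3% for five outcomes.

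**Step 2: all five required.** Under the same global null, the chance that all five are significant is below 2% at every ρ in the table. The result therefore turns on the missing success rule.

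**Step 3: several analyses of the cognitive scores.** This is an illustration only. It uses 99 per group, a baseline-to-follow-up correlation of 0.7, and modest correlations between outcomes. The stand-ins for the planned methods are a t-test, a baseline-adjusted comparison and a change-score comparison, with one t-test per biomarker. The chance of any significant result rises from 21.7% to about 30%. For the two cognitive scores alone it rises from about 9% to about 19%. This increase comes on top of the figures in step 1 and is not part of them.

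**Step 4: effect of the correction.** With DSST and MoCA tested by Holm, the first step is at 0.05/2 = 0.025. If the two are independent, the chance of any false positive is 1 − 0.975² = 4.9%. With all five kept, the first step is at 0.01, and 1 − 0.99⁵ = 4.9%.

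**Step 5: price in power.** Evaluable per group: 120 × 0.8 = 96. The difference detectable with 90% power, in SD units, is (z for the two-sided level + 1.282) × √(2/96), where √(2/96) = 0.1443:

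- at 0.05: (1.960 + 1.282) × 0.1443 = 0.47
- at 0.025: (2.241 + 1.282) × 0.1443 = 0.51
- at 0.01: (2.576 + 1.282) × 0.1443 = 0.56

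**The case against.** The strongest reply is that the protocol never says one significant outcome makes the trial positive. If all five were required, the error would not exceed 5%. This stands, and the 15–23% is conditional for that reason. It does not rescue the plan: an all-five rule is not stated either, and section 2.11.2 makes no provision for the power it would need.

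A reader might infer that success can be claimed on any of five outcomes by any of four methods. The text does not support this. Section 2.12.2 applies the four methods to the cognitive scores only. Counting the biomarkers as tested rests on their primary status and on the general sentence about the significance level. On explicitly stated between-group tests alone, with one test each, the figure is about 9–10%.

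A reader might also take the 15–23% to be the product of the repeated analyses. It is not, since it counts one test per outcome. Its lower end needs a correlation of about 0.7 across cognitive scores and plasma markers, which nothing in the documents supports.

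Finally, this is a condensed article and an analysis plan may exist. The exact biomarker test and the choice of a primary model could properly sit there, and the t-test with regression and the ANOVA with mixed model can be read as crude and adjusted versions of the same comparison. That is fair, and the absence of a biomarker test is not held against the protocol here. But the choice of primary outcomes belongs in the protocol, and an analysis plan that divided the significance level would contradict the article's statement covering all tests.

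**Conclusion.** The point holds in a conditional form. Five unordered primary outcomes with 0.05 for every test and no success rule do not control the long-term trial's error rate at 5%. If any one significant outcome counts as success, the familywise error with one test per outcome is 22.6% under independence and about 21%, 18% and 15% at assumed common correlations of 0.3, 0.5 and 0.7. For the two cognitive scores alone it is about 9–10%, so setting the biomarkers aside does not remove the problem. The unranked analyses and the second DSST visit raise the risk by an amount that the documents do not allow one to fix.

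The facts about the text are certain. The size depends on the success rule and the correlations, neither of which is stated. The point should be settled before unblinding, because a success rule chosen after results are seen would not be credible.

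**What to change.** In sections 2.8.2 and 2.12.2 and in the abstract:

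1. Keep DSST and MoCA at 24 months as the primary outcomes, which matches the cognition objectives in section 2.1. Test them with Holm at an overall two-sided 0.05: the smaller p-value against 0.025 and, if that passes, the other against 0.05.
2. Name one analysis for each: the 24-month group difference adjusted for the baseline score. For DSST this is a mixed model using both follow-up visits. For MoCA, which has only one follow-up value, it is ANCOVA.
3. Label the other analyses of the cognitive scores supportive, and tie the condition for the mediation analysis to the named primary analysis.
4. Move p-tau181, esRAGE and IL-6 to secondary, mechanistic outcomes, compared between groups with adjustment for baseline. If the sponsor wants them to stay primary, apply Holm across all five.
5. Restrict the general 0.05 sentence so that it does not override the Holm rule.

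**Cost.** No new visit, assay or participant is needed. It is, however, a substantive change to the primary outcomes of a registered trial. It needs a dated amendment to the protocol and the registration, with reasons, before unblinding. At 96 evaluable per group, the difference detectable with 90% power rises from about 0.47 to 0.51 SD at the first Holm step, or to about 0.56 SD if all five outcomes stay primary.
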